### Clinical Implications

The IMPRESS-AF trial will provide evidence on the clinical effectiveness of a readily available treatment in participants with AF. This large population of participants suffers markedly from reduced quality of life and is in clear need for additional therapies to improve their management. The data collected in this controlled trial dataset would achieve high external validity and will inform future guidance on the usefulness of spironolactone in this participant population. If our hypotheses were confirmed in this trial, IMPRESS-AF would provide a basis to roll out spironolactone therapy to prevent deterioration and improve symptoms and exercise capacity in these participants.

### Mechanistic aspects of spironolactone-mediated effects

|                          |            |               |            |       |          |
|--------------------------|------------|---------------|------------|-------|----------|
| Trial name:              | IMPRESS-AF |               |            |       |          |
| Protocol version number: | 6.0        | version date: | 12/10/2015 | Page: | 15 of 67 |

As mentioned in the introduction it is likely that antifibrotic effects of the spironolactone can play a clinically relevant role in the trial population. As previously suggested by the EME Board and in order to reduce costs of the project and to make the trial more straightforward and focused, we have removed the mechanistic parts of the trial (e.g. assessment of cardiac fibrosis using cardiac magnetic resonance imaging, laboratory measures, etc).

|                          |            |               |            |       |          |
|--------------------------|------------|---------------|------------|-------|----------|
| Trial name:              | IMPRESS-AF |               |            |       |          |
| Protocol version number: | 6.0        | version date: | 12/10/2015 | Page: | 16 of 67 |

---

## 2. AIMS, OBJECTIVES AND OUTCOME MEASURES

### 2.1 Aims and Objectives

The primary objectives of the trial are to determine if treatment with Spironolactone will improve exercise tolerance as a surrogate for cardiovascular mortality and morbidity, in participants with AF. The trial will also assess the effects of spironolactone on QoL and diastolic function, as well as rates of all-cause hospital admissions and spontaneous return to the sinus rhythm.

### 2.2 Outcome Measures

The **Primary** efficacy end point will be the improvement in exercise tolerance at 2 years. This will be assessed by the difference between trial groups in peak VO2 on CPET.

The **Secondary** efficacy end point will be the level of improvement in quality of life and diastolic function, and also the improvement the rate of all-cause hospital admissions and spontaneous return the sinus rhythm, with spironolactone. This will be assessed by:

- a) improvement in exercise tolerance measured by 6-minute walking test (a simple test of exercise performance) at baseline and at 2 years
- b) improvement in quality of life (using the validated Minnesota Living with Heart Failure [MLWHF] and EuroQol EQ-5D-5L [EQ-5D] questionnaires self-completed by participants, which will be completed at each months 12 and 24)
- c) improvement in LV diastolic function (E/E' on echocardiography) will be assessed at baseline and at 2 years
- d) improvement in rates of all-cause hospitalisations during 2 year follow-up.
- e) spontaneous return to sinus rhythm (ECG) after 2 years of treatment.

---

|                          |            |               |            |       |          |
|--------------------------|------------|---------------|------------|-------|----------|
| Trial name:              | IMPRESS-AF |               |            |       |          |
| Protocol version number: | 6.0        | version date: | 12/10/2015 | Page: | 17 of 67 |

### 3. TRIAL DESIGN

#### 3.1 Trial Design

This is a double-blind, 2 year randomised, placebo-controlled single centre trial, recruiting 250 participants from primary and secondary care. Eligible participants will present with symptoms of permanent AF levels and will be randomised to receive a 2 year treatment with either Spironolactone or placebo.

Prior to screening and recruitment of participants, the trial protocol will be finalised, practices recruited, research staff trained, initial eligibility screening in general practices undertaken to identify potential participants (Figure 3). Trial committees will meet to plan their respective committee charters and operating procedures.

Preliminary eligibility for the trial will be checked by the participants' GPs prior to patients being invited for the screening visit to the RC-CCS. Potential participants will be invited to attend an appointment at the trial site for an initial screening visit. They will be asked to bring their medication with them to the visit. At the screening visit, participants will be consented into the study and screened for eligibility. Eligible participants will be given the option of having the baseline visit straight after the screening visit or on a separate date. During the baseline visit, they will be randomised into the trial, subject to meeting the inclusion and exclusion criteria. Baseline parameters will be recorded. Participants will be randomised to receive a 2 year treatment with either Spironolactone or placebo and will be required to attend follow-up visits during the 2 year treatment period. The end of the trial will be defined as the date of the last visit of the last participant undergoing the trial.

After the recruitment the participants will have follow-up visits at 1, 3, 6, 9, 12, 15, 18, 21 months for assessment of clinical status, measurement of blood pressure, potassium, sodium, full blood count/hematocrit and renal function. Trial medication will be dispensed at baseline, 6 months, 12 months and 18 months. Quality of life will be assessed at baseline, 12 months and 24 months using the EQ-5D and the MLWHF questionnaires.

The final visit will be done at 24 months from the randomisation to assess the primary and secondary outcomes. The statistical analysis will be completed in year 4 of the trial (months 40-42).

#### 3.2 Trial Setting

Trial participants will be recruited from primary care AF disease registers (GP practices) as well as outpatient AF clinics (run by [name] [name] & [name]) in two large teaching hospitals: (i) City Hospital and (ii) Sandwell Hospital (the AF clinics).

This will allow enrolment of a representative population of patients with AF. The list of trial sites will be filed within the IMPRESS-AF Trial Master File (TMF).

|                          |            |               |            |       |          |
|--------------------------|------------|---------------|------------|-------|----------|
| Trial name:              | IMPRESS-AF |               |            |       |          |
| Protocol version number: | 6.0        | version date: | 12/10/2015 | Page: | 18 of 67 |

## 4. TRIAL POPULATION

### 4.1 Identification of participants

A total of 2560 potential patients will be screened within through Primary Healthcare Providers (i.e. GP Practices and Community Pharmacy). Screening will be within GP practices via GP registers. In addition, suitable patients from secondary care outpatient clinics will also be invited.

- Trial participants will be recruited from primary care AF disease registers as well as outpatient clinics in two large teaching hospitals
- PCCRTU will coordinate participant searches, using the clinical research network (CRN). The CRN will facilitate participant searches which will be carried out by staff at the GP practices. [name] [name] & [name] will identify suitable patients within their AF clinics
- The GPs will screen disease registers for participants with AF (with all of the inclusion and exclusion criteria applied), with the intention to screen 2560 potential participants.
- Potential participants (approximately 1280) who correspond to the trial requirements will be identified and invited to participate by their GP practice. Invitation letters and Patient Information Sheets will be sent to potential participants and will be produced by either a mail merge at the practice or via Docmail, a secure online mailing service.
- People who do not respond to the invitation letter within one calendar month will be sent a single reminder letter and Patient Information Sheet.
- Approximately 640 interested participants will reply to the Research Team at the University of Birmingham with an expression of interest to take part in the trial.

### 4.2 Eligibility

#### 4.1.1 Inclusion Criteria

- Age 50 years old or over
- Permanent AF as defined by the European Society of Cardiology (ESC) criteria

#### Inclusion criteria justifications:

To improve generalizability we do not include a requirement for evidence of diastolic dysfunction as the trial patients would have impaired diastolic function due to AF. Patients of both genders will be represented in the trial. Patients aged below 50 years will not be included as they represent a very small proportion (<10%) of patients with AF with HFpEF. This will provide a representative population of the targeted patients avoiding issues of possible pregnancies whilst on the trial medication.

#### 4.1.2 Exclusion Criteria

- Severe systemic illness with life expectancy of less than 2 years from screening
- Left ventricular ejection fraction (LVEF) <50% (echocardiography)
- Severe *chronic obstructive pulmonary disease (COPD)* (e.g., requiring home oxygen or chronic oral steroid therapy)
- Severe mitral/aortal valve stenosis/regurgitation
- Significant renal dysfunction (serum creatinine 220 µmol/L or above), anuria, active renal insufficiency, rapidly progressing or severe impairment of renal function, confirmed or suspected renal insufficiency in diabetic patients/ diabetic nephropathy
- Increase in potassium level to >5mmol/L
- Recent coronary artery bypass graft surgery (within 3 months)
- Use of aldosterone antagonist within 14 days before randomisation
- Use of or potassium sparing diuretic within 14 days before randomisation
- Systolic blood pressure >160 mm Hg

|                          |            |               |            |       |          |
|--------------------------|------------|---------------|------------|-------|----------|
| Trial name:              | IMPRESS-AF |               |            |       |          |
| Protocol version number: | 6.0        | version date: | 12/10/2015 | Page: | 19 of 67 |

- 
- Addison’s disease
  - Hypersensitivity to spironolactone or any of the ingredients in the product
  - Any participant characteristic that may interfere with adherence to the trial protocol
    - In-ability to understand and complete questionnaires (with or without use of a translator/translated materials).

---

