#### *Aldosterone and cardiac fibrosis*

Aldosterone is an important promoter of LV fibrosis. Mechanisms of aldosterone-mediated cardiac fibrosis include myocardial inflammation, oxidative stress, and cardiomyocyte apoptosis and also direct stimulation of cardiac fibroblasts to produce collagen. Clinical trials of aldosterone antagonists (RALES, EPHESUS, EMPHASIS-HF) uniformly showed their clinical benefits in systolic HF. Of note, according to a substudy of the RALES trial, the improved survival in participants treated by spironolactone was linked to its ability to reduce serum markers of ongoing fibrosis (type I and III collagen synthesis). Additionally aldosterone leads to cardiac invasion by proinflammatory mononuclear cells.

Cardiac expression of mineralocorticoid receptors is increased in AF, thus augmenting the genomic effects of aldosterone. Aldosterone antagonists (i.e., spironolactone or eplerenone) ameliorate LV fibrosis in animal models and reduce levels of serum markers of collagen turnover in humans with HFpEF (n=44). In a small, published pilot trial, spironolactone reduced LV fibrosis and improved diastolic function in participants with HFpEF (dilated cardiomyopathy, n=25).

In a previous randomised clinical trial on 102 participants with chronic kidney disease with normal cardiac contractility cardiac diastolic function was significantly improved over 40 weeks of treatment by 25 mg daily of spironolactone vs. placebo. Aldosterone inhibition with spironolactone significantly improves diastolic function and reduces cardiovascular stiffness in participants with chronic kidney disease. Recently, the same dose of spironolactone within 1 year significantly improved diastolic function in participants with HFpEF (the ALDO-DHF trial, but only 5% of participants [n=22] had AF).

***However no data are available on effects of aldosterone antagonists on diastolic dysfunction and exercise tolerance in AF.***

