## 6. ENROLMENT AND RANDOMISATION

### 6.1 Enrolment

#### Screening:

- Informed consent taken
- Eligibility criteria will be checked with the participant.
- Brain Natriuretic Peptide (BNP) level test using point of care device
- BP measurement
- If the participant has had blood tests performed at City Hospital within the 30 days preceeding the screening visit, results from these tests will be used for assessment at screening. If the results are abnormal and there is a clinical reason to repeat or no results are available for the patient, blood samples will be taken and the following tests performed: renal function, potassium, sodium, HBA1c (for diabetic patients only), lipid levels and full blood count (including hematocrit)
- Echocardiogram and ECG will be performed

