- Participants who meet the inclusion criteria will be invited to a baseline appointment and randomisation. They will be given the option of having the baseline appointment straight after the screening visit or at a later date. At the baseline appointment, eligibility, medical history and medication will be reviewed. Participants will be asked to bring their medication to every visit and told that, for participant safety, the appointment will not be able to go ahead without it. The participant will undergo standard clinical examination (including BP measurement), CPET and a 6 minute walking test. Quality of life questionnaires will be also completed (prior to randomisation). Participants' GPs will be informed of their participation in the trial.
- Double blinded block randomisation will be used to allocate participants to either a 2-year treatment with spironolactone or placebo, and trial medication will be dispensed.
- Following recruitment, all participants will be seen for follow-up visits at 1 month of randomisation and then quarterly during the 2 year follow-up period. All participants need to be seen within +/-1 week for month 1 visit and +/-2 weeks for all other follow up visits. Standard clinical examination (including BP measurement), concomitant medication review, blood samples will be taken at each of these follow-up visits to test renal function, potassium, sodium and full blood count (including hematocrit). IMP will be dispensed at months 6, 12 and 18 and QoL questionnaires will be completed at month 12.
- The participants will attend a final visit where the following will be done: standard clinical examination (including BP measurement), concomitant medication review, blood samples to test renal function, potassium, sodium and full blood count (including hematocrit),

|                          |            |               |            |       |          |
|--------------------------|------------|---------------|------------|-------|----------|
| Trial name:              | IMPRESS-AF |               |            |       |          |
| Protocol version number: | 5.0        | version date: | 12/10/2015 | Page: | 28 of 67 |

echocardiogram, ECG, BNP, CPET, 6 minute walk test. The QoL questionnaires will be completed.

- During the trial, should a test not be able to be performed, for example difficulty obtaining a blood sample or technical issues with equipment, participants will be asked if the visit can be rebooked.

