#### Blood test analysis

All clinical laboratory procedures will be undertaken by:

**Pathology Department, City Hospital, [name].  
[contact]**

Blood tests will be taken after patient written informed consent has been received and electronic requisitions will be completed. Specimens will be labelled as per Trust guidelines, a copy of the requisition will be retained.

Blood test results can be reviewed electronically, a copy will be printed. These will be reviewed and signed on a daily basis by the trials physician listed on the delegation log with this delegated duty

Blood samples will be used for routine laboratory checks done in City Hospital laboratory. With the participants consent, part of the blood samples will also be stored frozen in the study centre in City Hospital for future analysis of markers, which would help to better understand the study findings and mechanisms of the disease. Blood samples will not be used to perform any genetic analysis for this study.

For the screening visit, if blood test results are available from City Hospital Pathology Department which were obtained within 30 days of the screening visit, these test results will be used for

|                          |            |               |            |       |          |
|--------------------------|------------|---------------|------------|-------|----------|
| Trial name:              | IMPRESS-AF |               |            |       |          |
| Protocol version number: | 6.0        | version date: | 12/10/2015 | Page: | 31 of 67 |

---

assessment at screening. If the results are abnormal and there is a clinical reason to repeat the tests or no results are available, blood samples will be taken.

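### Eligibility bloods are dated to screening, not randomisation, so the potassium and creatinine exclusions can rest on results 30 or more days old at first dose

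*Protocol*

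**What the plan says.** **Exclusions.** Section 4.1.2 excludes people with potassium above 5 mmol/L or serum creatinine of 220 µmol/L or above. Its two drug exclusions are counted back from randomisation: "Use of aldosterone antagonist within 14 days before randomisation", and use of a "potassium sparing diuretic within 14 days before randomisation".

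**Bloods at screening.** The results that decide the potassium and creatinine exclusions have a different anchor. Section 6.1 says that, for tests done "within the 30 days preceeding the screening visit, results from these tests will be used for assessment at screening". New samples are taken only if there are no such results, or if they are abnormal and there are clinical grounds to redo them. Section 8.2 (Blood test analysis) repeats the rule. Section 8.1 lists a blood sample at the screening visit without mentioning this alternative.

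**Gap to baseline.** Section 8.1 says of those who qualify: "They will be given the option of having the baseline appointment straight after the screening visit or at a later date". Section 3.1 says the same in other words. Visit windows are given for follow-up visits only.

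**Baseline visit.** The assessment table at the start of section 8 marks an eligibility check at baseline. Its row for renal function, potassium and sodium is marked at screening and from month 1 onward, not at baseline. The baseline list in section 8.3 contains no blood test. Section 7.2, however, says that potassium and renal function are monitored at every visit, and Appendix 1 describes blood collected at randomisation, for biomarkers.

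**Echocardiogram.** Section 6.1 and the table place it at screening and month 24. Section 2.2 says E/E' is assessed at baseline and at two years.

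**The concern.** An eligibility limit on a laboratory value protects the participant only if the value is current when treatment starts. Here the age limit runs to a visit that may precede treatment by any interval, and the eligibility check at randomisation has no new laboratory result to check. Someone whose potassium or creatinine has crossed the limit since the sample would be randomised and dispensed trial medication, and the change would first be seen at month 1.

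This is out of step with the protocol's own monitoring, since section 7.2 asks for bloods within a week of any dose adjustment. A participant whose potassium had risen to 5.1-5.5 mmol/L since the sample would meet the dose-reduction trigger in section 7.2 on the day of the first dose, without anyone knowing.

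A lesser issue comes from the same mismatch of dates. The drug-free period is tied to randomisation, while the only pre-treatment echocardiogram is tied to screening. The document does not say which measurements that period is meant to cover.

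**Working it through.** **1. Age of the eligibility bloods at randomisation**

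Inputs:
- look-back before screening: 30 days (sections 6.1 and 8.2);
- gap g from screening to baseline: 0 days or more, no stated maximum (sections 3.1 and 8.1);
- potassium or renal tests at baseline: none (section 8 table; section 8.3);
- next test: month 1, ±1 week (section 8.1).

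Maximum age = 30 + g days.
- g = 0: 30 + 0 = 30 days.
- g = 15 (illustration): 30 + 15 = 45 days.
- g = 60 (illustration): 30 + 60 = 90 days.

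Only the first line rests on the protocol's figures alone, because the document gives no distribution of g. Taking month 1 as about day 30, the latest in-window visit is about day 37. Two consecutive results can then be 30 + g + 37 = 67 + g days apart, or 67 days with a same-day baseline.

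**2. Which measurements can fall before the 14-day drug-free period**

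A measurement can fall before it when its age at randomisation exceeds 14 days.
- Bloods: the maximum age of 30 + g exceeds 14 for every g, including 0.
- Echocardiogram: the age is g, so only when g exceeds 14.
- CPET, walk test and quality of life: measured at the baseline visit, so inside the period.

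**3. Effect on the E/E' comparison**

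The plan's own figure first. Section 13.1.1 uses a difference of -3.2, SD 2.08 and 100 per group. SE = 2.08 × √(2/100) = 0.294, and the 95% CI is -3.2 ± 1.96 × 0.294 = -3.78 to -2.62. This matches its table, and the stated power above 99% is reproduced.

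Now assume that a fraction f of each arm has a screening E/E' already lowered by the full 3.2, and that this effect is lost off drug.
- Mean change on spironolactone: -3.2 + 3.2f.
- Mean change on placebo: 0 + 3.2f.
- Difference: -3.2 for any f.
- SD of change: √(2.08² + f(1 - f) × 3.2²).

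| f (assumed) | SD | SE | Power for 3.2 |
|---|---|---|---|
| 0.05 | 2.19 | 0.31 | above 99% |
| 0.10 | 2.29 | 0.32 | above 99% |
| 0.20 | 2.44 | 0.35 | above 99% |

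The document gives no value for f, so the table shows a range.

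**The case against.** **The defence of the current text.** GPs apply the criteria at the register search (section 4.1). Eligibility is checked at screening and again at baseline, and participants bring their medication to visits. Abnormal earlier results can be repeated. Section 7.2 can be read as requiring bloods at baseline, many participants may take the same-day option, and the trial schema, which cannot be read here, might carry a window.

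These points bear on how often the problem arises, which the document does not quantify. They do not remove it. A register search and a medication review give no new potassium or creatinine value. The same-day option still allows a 30-day-old result. The sentence in section 7.2 is at odds with the table and the baseline list, so it cannot settle the matter until they are reconciled.

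**A stronger reading that the documents do not support.** A reader might infer that an echocardiogram taken on an aldosterone antagonist would bias the E/E' result. An on-drug value arises before randomisation and should fall equally on both arms. It blurs change within each arm, but the between-group difference, which is what section 13.1.1 powers, stays where it was. The case is also permitted rather than shown to be common: no procedure in the protocol stops such a drug so that someone can qualify. The -3.2 itself comes from what the reference list shows to be an exercise-training study, so it does not measure residual drug effect.

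Nor do the documents show that 14 drug-free days before the echocardiogram would give a clean baseline. Section 1.1 reports that diastolic function was "significantly improved over 40 weeks of treatment by 25 mg daily of spironolactone" and gives no rate at which such an effect fades.

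BNP is also measured at screening, but it is neither a listed outcome nor a current eligibility criterion, so nothing turns on its date.

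**Conclusion.** The point holds as a matter of eligibility, safety and internal consistency. Followed as written, the protocol lets two laboratory exclusions be judged on a result 30 days old in the most favourable visit pattern. With a delayed baseline the result can be older, without a stated limit, and no further test is scheduled until month 1. Sections 7.2 and 8 disagree on whether any potassium or renal test belongs to the baseline visit.

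It is not a threat to the efficacy conclusions. Peak VO2, the walk test and quality of life are measured at baseline. For E/E' the cost is a small loss of precision: the SE goes from 0.29 to at most 0.35 over the assumed range of f, with power still above 99%.

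The conclusion assumes that the unreadable schema states no window from screening to randomisation. The 67-day spacing also takes month 1 as about 30 days.

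**What to change.** 1. In sections 6.1 and 8.2, count the validity of eligibility bloods to the date of randomisation. The interval is for the sponsor to set, and none is proposed here.
2. Reconcile sections 3.1, 6.1, 7.2, 8.1, 8.2 and 8.3 and the assessment table, so that the baseline eligibility check has an in-date potassium and renal result. They should also agree on whether a sample is always taken at screening. The blood draw at randomisation in Appendix 1 should be brought into line at the same time.
3. Reconcile section 2.2 with the screening-only echocardiogram by stating which recording is the baseline E/E'. In section 4.1.2, state which measurement dates the drug-free period must cover.

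**Cost.** Mostly wording, plus a repeat routine blood test for participants with a long gap between screening and baseline. It may not always be free of extra attendances: samples go to the hospital laboratory and results are reviewed daily, while randomisation and dispensing happen at the baseline visit. Some participants may need an earlier blood draw or a postponed visit.
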